### Proposed Intervention Components

#### MES

The MES is a web-based mobile asthma management intervention delivered via the Computerized Intervention Authoring Software (CIAS 3.0) platform [40] on participants’ personal mobile devices. Despite being an automated mobile program, the MES is *tailored* for each participant in several ways. First, at baseline, participants will be classified according to their Asthma Self-Regulatory Development stage [41], which will guide behavioral content and number of sessions that each receives. Second, the MES is an interactive program that is individualized based on MI principles and participant-selected barriers/goals. Third, participants receive personalized feedback based on their responses to a daily diary completed between sessions 1 and 2, which prompts for barriers and facilitators to daily asthma management and control. Fourth, delivered content is based on a computer algorithm that incorporates the stage of asthma self-regulation to determine the number and frequency of sessions. Sessions are provided by an animated character (avatar) developed via focus groups with African Americans. Significant efforts have been made to ensure that the avatar delivers the intervention in a way that engages AAEAs with empathy, optimism, and autonomy support. The MES focuses on asthma management behaviors with feedback on asthma symptoms, physical activity, adherence, and tailored education. The avatar evokes both importance and confidence (key components of motivation) with MI strategies, such as identification of the benefits of behavior change, affirmations to reinforce change talk and boost confidence, and identification of personal strengths and resources. The avatar reflects (summarizes what the participant is saying to convey understanding) without judgment and provides statements to emphasize autonomy. Participants will follow a 4-step sequence of problem-solving based on the principles of the social cognitive theory, particularly self-regulation, and MI. This will include problem selection, self-observation with an online diary, goal selection, barrier selection, and reward selection, as participants progress through the 4 sessions (Figure 3).

**Figure 3 figure3:**
[figure not shown]
Flow of motivational enhancement system and supportive accountability intervention components.

#### SA

SA is an asthma management intervention delivered by asthma nurses trained in targeted MI skills (eg, open-ended questions around change talk and affirmations) via participants’ personal mobile devices (eg, Skype, FaceTime, voice calls, and SMS text messages). The theory underlying SA is that education and behavior change are most impactful when delivered by a knowledgeable yet supportive authority figure (ie, nurse) [42]. SA and the MES will be matched for number, timing, and focus of sessions. Sessions include promoting motivation for asthma management, education, feedback from participant reports of symptoms and management behaviors, enhancing self-efficacy, and goal setting. A total of 4 discrete sessions, as well as an asthma online diary, will be used in the SA intervention. SA sessions will also provide real-time exploration of barriers and problem-solving around asthma management, and will allow greater flexibility than the MES because they are delivered by a nurse interventionist versus an automated program. For instance, participants can choose topics beyond those on the MES list of most commonly chosen problems. SA calls include scripted components to check-in on asthma management activities but are otherwise flexible to allow focus on tailored barriers and issues a participant may have surrounding asthma management and control.

Asthma nurses will be provided with training in tailored MI. The following 3 provider communication behaviors have been found to be the strongest predictors of patient change talk: emphasizing patients’ autonomy, open-ended questions to elicit change talk, and reflections of change talk [43-45]. For this study, it is not feasible to train nurses to full MI competency, so our team has developed an approach to provide training in fundamental MI skills linked to behavior change [43]. Training will be provided by trainers certified by the Motivational Interviewing Network of Trainers and will include an initial 2-day workshop, followed by fidelity monitoring and boosters. MI fidelity will be monitored through audio recordings from SA sessions and rated using the MI Coach Rating Scale (MI-CRS) [46]. The MI-CRS is a 12-item measure of MI competence. Nurses will be trained in the interpretation of data from study-provided smart watches and will use this to encourage activity and asthma management.

#### TXT

SMS text messages will target asthma knowledge. These messages will be sent via CIAS 3.0 to participants’ personal mobile devices with facts about asthma management, links to educational web content, and videos providing information about living with asthma. A library of asthma education text messages developed during previous work will be refined and expanded using information from the CDC “Learn how to Control your Asthma” website [47]. Information covered includes “What is asthma,” “What is an asthma attack,” “What causes an asthma attack,” “How is asthma treated,” “Asthma and weather,” “Using an inhaler,” “Using a spacer,” and “Asthma action plans.” Messages will be sent twice a week for 4 weeks and then once a week for 4 weeks. SMS text messages will be formatted to fit a smart watch (see below) so that participants can use the study-provided device.

#### PAT

All participants, including those in the control arm, will be provided a smart watch in the form of an Apple Watch or Android watch. This PAT device will allow participants to accurately track exercise and total steps each day [48]. The US 2018 Physical Activity Guidelines Advisory Committee Scientific Report found “moderate” to “strong” evidence that mobile phones and wearable devices increase physical activity [49]. Through PAT, users will be able to set daily goals and attain or improve motivation to continue asthma management. For individuals randomized to groups that also include the MES or SA, those programs will incorporate PAT data that are remotely transmitted, to facilitate asthma management motivation. In formative work, AAEAs were enthusiastic regarding interventions that provided users a smart watch, and stated they were much more likely to continue in a trial that did so.

### Intervention Component Refinement

The MES, SA, and SMS components have been developed in previous work with different patient populations and behavioral targets. The current protocol includes 2 phases. During Phase 1 of the project, all 3 components will be refined and beta-tested for use with AAEAs having uncontrolled asthma. Minor adjustments will be required as we will now be integrating components both alone and in combination. Additionally, component refinement will be achieved with significant input from relevant stakeholders. Stakeholders include AAEAs with asthma, asthma nurses, asthma educators, primary care physicians, asthma specialty physicians, and computer specialists. All content has been developed through multi-step formative work, but it is important to continue to refresh and update content (eg, changing asthma guidelines and social phenomenon). For the primary stakeholder (AAEAs with asthma), 3 focus groups (4-6 individuals per group) will be held; the specifics of each component to be discussed are described below. Finally, prior to evaluation in the trial, beta-testing with a group of 10 AAEAs with asthma will be performed for each component arm to ensure that combinations are acceptable and well-integrated. Beta-testers will be asked to use assigned components, followed by an interview to obtain feedback on content, delivery, and technological issues.

### Qualitative Data Analysis

We will utilize a systematic, yet flexible, approach to thematic analysis to maintain rigor within the study timeline. Data will be managed and coded using NVivo 12. Two members of the research team will utilize the Framework Method, now used widely in health research [44-46,49-52]. Its defining feature is the matrix output, providing a structure to systematically reduce the data for analysis on various levels. After transcription, analysis will proceed through several stages: (1) familiarization with the session; (2) thematic coding; (3) developing a working analytical framework; (4) applying the framework; (5) charting data into the framework matrix; and (6) interpreting the data.

### Study Trial Design

This project will use the MOST [53-55] framework to optimize a mobile intervention to enhance the asthma management behaviors of AAEAs. The MOST design allows the evaluation of not only efficacy, but also efficiency, economy, scalability, and sustainability [56]. We will first refine the intervention components (MES, SA, PAT, and TXT) based on input from key stakeholders, including asthma nurses and AAEAs with asthma. We will then conduct a component selection experiment using a factorial research design to build an intervention that has been optimized for maximum efficacy. We will use a clinically significant improvement in asthma control (a change of ≥3 on the ACT [35]) as the criterion for determining which components should be kept in the optimized intervention. During the study, participants, their physicians, and any members of the study team who are adjudicators of outcomes will be unaware of study group assignment to the extent possible in a behavioral trial.

This study will use a 6-arm incomplete factorial design for the component selection experiment (Table 1). A full factorial design will not be used as some of the experimental combinations cannot be present simultaneously (eg, MES and SA are mHealth and involve human delivery of the same intervention content, and therefore logically cannot be combined), and PAT will be provided to all participants. Byar et al [57] described such incomplete designs, and in particular, we are employing “Design 3,” which is a “2^3^ − Y_AB_ − Y_ABC_” design. This design matches with our experimental combination as MES (A) and SA (B) components cannot occur together. Table 1 shows the incomplete factorial design given the possible combinations of the 4 components [55]. As the full factorial design is not feasible for the current setup, we also considered a 2^3−1^ fractional factorial design with 3 factors but with 4 (2^3−1^) treatment conditions, allowing aliasing of the highest-level interaction (ie, each main effect will be confounded with a 2-factor interaction). However, our design with 6 components is a superset of that 2^3−1^ fractional factorial design and will result in better evaluation of treatment combinations than any fractional factorial (see the study by Byar et al [57]). This design preserves much of the full factorial structure and provides more reasonable results than a fractional factorial design [58]. This design also allows evaluation of the main effect of each component and exploration of interaction effects when components are combined, though more assumptions are needed as a full factorial (=2^3^) is not present. One assumption is a “saturated design” when the combination missing (AB and ABC) is assumed to be 0 or have no effect. The component selection experiment is powered for the main effects and will include 180 participants (or 30 participants per arm).

**Table 1 table1:** Intervention conditions.

Experimental condition	Motivational Enhancement System	SMS text messaging	Supportive accountability	Usual care	Physical activity tracking
1	Yes	No	No	No	Yes
2	No	Yes	No	No	Yes
3	No	No	Yes	No	Yes
4	Yes	Yes	No	No	Yes
5	No	Yes	Yes	No	Yes
6	No	No	No	Yes	Yes

### Study Procedures

All data collection and intervention activities will take place remotely. Following enrollment, research assistants will contact participants for consent and onboarding/orientation. Participants will receive US $25 per assessment for a total of US $100 and keep the Apple or Android watch. Participants will receive US $50 per month during the 2-month intervention period to offset the cost of their cell phone bill. To enhance engagement, this incentive will only be offered if participants remain above a determined threshold of response (eg, answer 80% of SA calls, text messages, etc), to be determined by key stakeholders during focus groups [59]. Data collection and most intervention activities will be conducted using CIAS 3.0. CIAS 3.0 is an HTML5 mobile web app with a responsive design capable of being deployed on any web browser accessed via any device (eg, Apple or Android smartphones) of any size (ie, auto reformat for optimal viewing on any size screen). This mobile version has an enhanced feature set, including improved voice quality for narrated content and appearance. Data collection sessions will take less than 30 minutes to complete. Participants will be randomized following baseline. Because the assessment is computer administered, there is no data collection staff per se for written measures.

#### Randomization

Participants will be randomized to 1 of 6 study arms following baseline. Randomization will be stratified by sex as we expect 65%-70% of subjects to be female (given the demographics of asthma among AAEAs). We will randomize using permuted blocks with sex as a stratification variable. Permuted blocks have the advantage of ensuring a balance between treatment arms for important prognostic variables without unmasking the next treatment allocation [60]. The randomization program/code will be developed and maintained centrally by a biostatistician.

#### Measurement

Data collection will occur at baseline, 3 months (postintervention), 6 months, and 12 months. At baseline, demographic information, asthma-specific information, and psychosocial information will be collected. The primary outcome will be improvement in asthma control as assessed by the ACT [35,61]. The mediators of asthma control will be based on the evaluation of IMB and SRT constructs, including asthma knowledge, attitudes, motivation, self-management behaviors, and self-efficacy.

Although we have feasibility data for the individual components, we will now obtain data for component combinations. Questionnaires and qualitative methodology will be used to determine recruitment and retention, adherence to the program, suitability and variability of outcome measures used, application and fidelity of the program, and demand/acceptability of the program for patients and professionals [62].

### Statistical Analysis

We will initially characterize the data heterogeneity and frequency distributions of asthma control, the primary outcome, and all secondary outcomes (asthma management and IMB/SRT constructs). We will check for out-of-range values, outliers, and abnormal values using graphical methods and create descriptive summaries to ensure that all values are within expected ranges. Unexpected findings will prompt checking of raw data for accuracy of data entry and recording. We will analyze the effect of the intervention components on the longitudinal measures of asthma control (ACT) using a mixed effects linear model for repeated measures analysis of variance (ANOVA) of a factorial design. This model will include a fixed effects indicator for each intervention component (SA, MES, TXT, and PAT) and time, along with all interactions with time. Random intercepts will be used to account for the longitudinal nature of the data. Before evaluating which components contribute to a potential change in the ACT score, we will use the model to compare the treatment with all 3 components and the control condition to determine whether the complete intervention is efficacious. If this statistical test is significant, we will identify those components that result in a significant change in the ACT score by examining the interactions between the main effects and time using the strategy advocated by Collins et al [53], which begins with the simplest effects and only adds higher-order interactions if needed. We will use a *P* value of <.05 for the test of total effect (difference between the treatment with all 3 components and the control treatment) and .1 to identify which components contribute to the total effect. We will use a higher threshold for the component selection test because we want to reduce the likelihood of not selecting a component that is contributing to the total effect. Secondary outcomes will be analyzed using a similar approach, but they are not powered. If significant baseline group imbalance is detected for any variable and its correlation with the outcome is 0.30, that variable will be included as a covariate in the inferential analyses. Dropouts and completers will also be compared in terms of baseline variables.

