### Study Aims

The purpose of this study is to develop an effective mHealth intervention to improve asthma management and asthma control among AAEAs. We have developed and tested technology-based theoretically grounded asthma self-management interventions for AAEAs that will be refined and evaluated as components of a resulting mobile asthma management intervention. These intervention components are based on the SRT or IMB model, and utilize MI. We will evaluate 4 intervention components for synergistic effects. The first component is the Motivational Enhancement System (MES) for asthma management. The MES is a mobile 4-session MI intervention using supported self-regulation to enhance motivation for asthma management and asthma knowledge. Personalized content is chosen by a computer algorithm, and is based on each participant’s self-regulation stage, activity level, daily experiences, and goals. The second component is supportive accountability (SA). SA is administered by asthma nurses using targeted mobile support (Skype/voice calls) to provide education, promote self-efficacy, and overcome barriers through an MI-based framework. The third component is SMS text messaging (TXT). It provides asthma management education. The fourth component is physical activity tracking (PAT). PAT uses wearable technology (eg, a smart watch) for meeting user-defined activity goals as part of the asthma management regimen.

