Participants will be recruited from multiple sites of the American Lung Association-Airway Clinical Research Centers network and clinics at Wayne State University/Detroit Medical Center and the University of Michigan. Participants (N=180) with uncontrolled persistent asthma will be randomized to 1 of 6 intervention arms consisting of combinations of the 4 components through a multiphase optimization strategy (MOST) design. The MOST design is an innovative, and cost- and time-effective experimental design that utilizes engineering principles to test behavioral interventions. The MOST design uses an optimization criterion to make decisions and refine the efficacy of each of the intervention components. We will adopt clinically significant improvements in asthma control (defined as a change of ≥3 on the Asthma Control Test [ACT]) as an optimization criterion in a component selection experiment using a randomized factorial design. This experiment is equivalent to conducting multiple pilot randomized clinical trials to evaluate the efficacy of each component, yet uses only a fraction of the sample size, resources, and time. At the completion of this study, we will have developed an empirically supported mobile asthma management intervention to improve asthma control for high-risk AAEAs.

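### The primary model includes activity-tracking (PAT) terms, but every arm receives PAT, so its effect cannot be estimated and only three of the four named components can be tested

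*Protocol article*

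**What the plan says.** All references are to the protocol article.

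- **Statistical Analysis.** The mixed model for repeated ACT scores is to contain "a fixed effects indicator for each intervention component (SA, MES, TXT, and PAT) and time, along with all interactions with time". If a first test of total effect reaches P<.05, components are identified from their interactions with time at a threshold of .1.
- **Study Trial Design.** The text says "PAT will be provided to all participants", as one reason for not using a full factorial. Table 1 has Yes in the PAT column for all six conditions, including condition 6 (usual care).
- **PAT.** "All participants, including those in the control arm, will be provided a smart watch".
- **Study Aims.** "We will evaluate 4 intervention components for synergistic effects", with PAT listed as the fourth. The experiment is likened to several pilot trials run "to evaluate the efficacy of each component, yet uses only a fraction of the sample size, resources, and time".
- **Study Trial Design, on what the design delivers.** "This design also allows evaluation of the main effect of each component".

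The incomplete factorial named in Study Trial Design has three factors: MES, SA and a third that can only be TXT. PAT is not one of them. Statistical Analysis itself later speaks of a treatment with three components.

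**The concern.** A factor that takes the same value in every arm carries no randomized information. The article nevertheless enters PAT in the primary model as if it varied, and counts it among the components whose efficacy and synergy the trial will establish.

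Two things are at stake. First, the model cannot be fitted as stated: the analyst must drop terms that the plan requires, and the article does not say which. Second, the purpose of the experiment is to decide which components stay in the optimized package. PAT is on that list with no comparison behind it, so whether it stays or goes cannot be a finding of this trial.

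**Working it through.** **Inputs.** Arms and components come from Table 1, with 1 for Yes and 0 for No. Visits are baseline, 3, 6 and 12 months (Measurement). The fixed effects are those in Statistical Analysis, reading the interactions as component by time. Size is 30 per arm.

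**Stated size.** 6 arms × 30 = 180, as the article says; 180 × 4 visits = 720 rows. Nothing below depends on this number.

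**Allocation from Table 1.**

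| Condition | MES | TXT | SA | PAT |
|---|---|---|---|---|
| 1 | 1 | 0 | 0 | 1 |
| 2 | 0 | 1 | 0 | 1 |
| 3 | 0 | 0 | 1 | 1 |
| 4 | 1 | 1 | 0 | 1 |
| 5 | 0 | 1 | 1 | 1 |
| 6 | 0 | 0 | 0 | 1 |

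Since PAT = 1 in every row:

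- PAT = intercept
- PAT × time = time, at each visit
- PAT × MES = MES, PAT × SA = SA, PAT × TXT = TXT

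The last line shows that synergy between PAT and any other component is not estimable either.

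**Columns and rank.** The article does not say whether time is categorical or linear, so both were checked.

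| Time | PAT in model | Columns | Rank | Deficiency |
|---|---|---|---|---|
| Categorical | Yes | 1 + 4 + 3 + 4 × 3 = 20 | 16 | 4 |
| Categorical | No | 1 + 3 + 3 + 3 × 3 = 16 | 16 | 0 |
| Linear | Yes | 1 + 4 + 1 + 4 × 1 = 10 | 8 | 2 |
| Linear | No | 1 + 3 + 1 + 3 × 1 = 8 | 8 | 0 |

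**Which coefficients are affected.** Each column of the 20-column matrix was deleted in turn. A coefficient is estimable only if deleting its column lowers the rank.

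- Not estimable: PAT and PAT × months 3, 6 and 12. While PAT is in the model, the intercept and the three time effects are not separately estimable either.
- Estimable: MES, TXT, SA and all nine of their interactions with time.

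**What six arms can carry.** Intercept + 3 main effects (MES, TXT, SA) + MES × TXT + SA × TXT = 6 parameters, rank 6. The arms are then used up, with no degree of freedom left for PAT.

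**Recoding does not help.** Setting PAT to 0 at baseline and 1 afterwards only makes it identical to the before-after time effect. Nor does a larger sample or a different significance level, because the column remains constant across arms.

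**The case against.** The strongest reply is that the randomized analysis is intact. The design named in Study Trial Design has three factors, the article openly says that PAT goes to everyone, and redundant columns do not alter the estimates, standard errors or P values for MES, SA and TXT. This stands, and it limits the harm. It does not remove the error: universal provision is given only as a reason against a full factorial, and neither the PAT terms nor the claims about four components are withdrawn. An analysis plan that is not shown could repair the model, but it could not make the article's claims about PAT true.

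A reader might go further and infer that PAT is likely to be selected wrongly: participants enter with ACT below 19, scores drift up by regression to the mean, and the software prints that drift as PAT-by-time. The documents do not support this as an expected result.

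- It requires the software to keep PAT-by-time and drop time. In the order the article lists the terms, retention from left to right would keep time and drop PAT-by-time.
- Components are examined only after the total-effect test passes at P<.05. That test compares arms that all have PAT, so PAT and regression to the mean cancel. If nothing works, it passes in about 5% of trials, which caps any false selection of PAT near 5%.
- The size of any drift would need an ACT mean, SD and retest correlation, none of which the article gives.

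A reader might also infer that the control arm is misdescribed, or that the Discussion promises a test of PAT. Table 1 shows PAT and usual care together in condition 6. The Discussion speaks of the role of physical activity, which is a behavior, and makes no claim to test the tracker.

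**Conclusion.** The point holds as a specification error and an over-claim about PAT. The primary model is over-parameterized by 4 terms with categorical time, or 2 with linear time. Three of the four named components can be evaluated. PAT's main effect, its synergy with the others and its place under the selection rule cannot. The statements in Study Aims and Study Trial Design that cover four components, or each component, are wrong for PAT.

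This rests only on Table 1, the PAT section and the stated model; no assumption about ACT scores is needed. The MES, SA and TXT contrasts are unaffected, but they are effects added to PAT. The PAT section also says that MES and SA use the transmitted tracker data, so the trial does not show how those two would perform without it.

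**What to change.** 1. In Statistical Analysis, remove PAT and PAT-by-time from the model, leaving MES, SA, TXT, time and their interactions with time.
2. State that three components are tested on a constant PAT background, and that PAT is not subject to the selection test.
3. Correct Study Aims (the claim on four components and synergy, and the claim on each component's efficacy) and Study Trial Design (the main effect of each component) to match. Adjust the wording on testing components in the Methods part of the Abstract.
4. State that any overall change over time, including change in the control arm, must not be read as an effect of PAT.

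Relabelling condition 6 as PAT plus usual care would be clearer but is optional.

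The cost is text edits only; allocation, data collection and sample size stay as they are. The one concession is that the stated number of tested components falls from 4 to 3.

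### With random intercepts as the only stated correlation device, the .05 and .1 test levels are unprotected if ACT correlation falls with time or its variance differs between visits

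*Protocol article*

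**What the plan says.** All of the following is in the protocol article; no separate analysis plan is shown.

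- **Model.** Statistical Analysis plans to analyse ACT "using a mixed effects linear model for repeated measures analysis of variance (ANOVA) of a factorial design". The fixed part is stated as: "This model will include a fixed effects indicator for each intervention component (SA, MES, TXT, and PAT) and time, along with all interactions with time".
- **Within-person correlation.** The one statement is "Random intercepts will be used to account for the longitudinal nature of the data". No random slope, residual covariance structure or robust standard error is mentioned.
- **Visits.** Measurement: "Data collection will occur at baseline, 3 months (postintervention), 6 months, and 12 months".
- **Decision rule.** The gate is a P "value of <.05 for the test of total effect", "and .1 to identify which components contribute to the total effect". Components are then judged by "examining the interactions between the main effects and time using the strategy advocated by Collins et al". The text does not say whether time is categorical or linear, or which visit or trend decides.
- **Entry.** Study Participants and Setting requires an ACT score below 19 at entry. Follow-up scores have no such limit.

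**The concern.** A random intercept with independent residuals implies compound symmetry: one variance for all visits and one correlation for every pair. Two features of this trial make that doubtful. Visit gaps run from 3 to 12 months, and asthma control may well be more alike at visits close together. The entry rule also truncates baseline ACT, so the baseline variance is probably smaller than the follow-up variance.

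Both the gate and the component tests are component-by-time effects, so they are contrasts of within-person change. Under the stated model, every such contrast takes its standard error from one pooled residual variance. If correlation decays, that pooled value is too small for changes over 12 months or for a time trend, and too large for change over 3 months. An inert component could then be kept too often on late or trend evidence. A useful one could be missed just after the intervention. Choosing components is the purpose of the experiment, so the levels of these tests matter.

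**Working it through.** **Inputs from the article.** Visits at 0, 3, 6 and 12 months; levels .05 and .1 (two-sided assumed); six arms, 180 participants, 150 after attrition (25 per arm); random intercepts.

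**Inputs assumed.** The article gives no ACT correlation or SD. With *g* the gap in months, the correlations tried were:
- A: .8^(g/3)
- B: .7^(g/3)
- C: .4 + .6 × .5^(g/3)
- D: .4 + .4 × .8^(g/3), leaving 20% noise
- E: .3 + .3 × .8^(g/3), leaving 40% noise (weak decay)
- F: constant .5

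Each was tried with equal SDs and with the baseline SD at 0.75 of follow-up.

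**Formula (balanced data, large sample).** For a time contrast *c* summing to zero and true covariance *V*:
- true variance: c′Vc
- variance used by the random-intercept model: s²·c′c, with s² = (tr V − 1′V1/4)/3
- ratio: R = c′Vc / (s²·c′c)
- actual level: 2·[1 − Φ(z/√R)], with z = 1.645 for .10 and 1.960 for .05

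The between-arm part of each test multiplies both variances equally and cancels. The result is therefore the same for any component, and for the total effect however it is formed from the arms.

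**Stated levels reproduced.** Under F with equal SDs, s² = (4 − 10/4)/3 = .5 and R = 1 for every contrast, so the levels are .10 and .05 as stated.

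**Worked case, pattern A, equal SDs.** The six correlations are .8, .64, .4096, .8, .512 and .64, which sum to 3.8016.
- 1′V1 = 4 + 2 × 3.8016 = 11.6032; s² = (4 − 2.9008)/3 = .3664; model variance for any two-visit difference = 2 × .3664 = .7328
- 12 v 0: true 2 − 2 × .4096 = 1.1808; R = 1.61; level .195 for .10 and .123 for .05
- 3 v 0: true 2 − 2 × .8 = .40; R = .55; level .026 and .008
- Linear trend: R = 1.80; level .220 and .144

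**Actual level of a nominal .10 test, equal SDs**

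| Pattern | 3 v 0 | 6 v 0 | 12 v 0 | Trend | Mean post v 0 |
|---|---|---|---|---|---|
| A | .026 | .097 | .195 | .220 | .116 |
| B | .033 | .101 | .179 | .203 | .111 |
| C | .049 | .107 | .150 | .170 | .105 |
| D | .067 | .099 | .143 | .155 | .107 |
| E | .083 | .099 | .122 | .129 | .103 |
| F | .100 | .100 | .100 | .100 | .100 |

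**Same, baseline SD 0.75 of follow-up**

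| Pattern | 3 v 0 | 12 v 0 | Trend | Mean post v 0 |
|---|---|---|---|---|
| A | .026 | .167 | .201 | .084 |
| B | .028 | .152 | .186 | .076 |
| C | .042 | .126 | .155 | .071 |
| D | .059 | .121 | .142 | .077 |
| F | .082 | .082 | .093 | .065 |

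For the nominal .05 test with equal SDs, patterns A to D give .081-.123 at 12 months, .090-.144 for trend and .008-.029 at 3 months.

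**3-df tests.** These were simulated: 10,000 null trials per pattern, 25 per arm, the six arms of Table 1, MES, TXT and SA coded. PAT was left out because every arm receives it. Under A, B, C and one further decaying pattern (.2 + .8 × .7^(g/3)), with equal SDs, the component-by-time test ran at .100-.115 for .10. The total-effect test ran at .054-.063 for .05.

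**The case against.** A reader might infer that the tests simply fail their stated levels. The documents do not support that. They give no ACT correlation, SD or slope variance, and if correlation and variance are constant all levels are exact.

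Nor does the article name the contrasts where the large figures arise. A repeated-measures ANOVA with four visits most naturally suggests a 3-df component-by-time test, which is barely affected. With equal variances, 6 months against baseline and the post-baseline mean against baseline also stay close to nominal. The likely smaller baseline variance reduces the 12-month inflation and makes some contrasts conservative. All of this stands, and it limits the point to a conditional one.

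It can also be said that a condensed article leaves residual structure and degrees of freedom to the analysis plan, and that the random-intercept sentence does not exclude a further structure. That is fair as to missing detail. But the sentence is a positive choice of method, and the only one given for this purpose, so it needs to be confirmed or replaced.

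Finally, this is a screening experiment with a deliberately lenient .1. That lowers the stakes but does not remove them. The leniency was set at .1 so as not to drop a contributing component. A test that in fact runs at .20 is not that choice, and one that runs at .03 at 3 months works against it.

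**Conclusion.** The point holds in conditional form. The stated covariance does not protect the .05 and .1 levels if ACT correlation falls with time or if variances differ between visits; size and direction depend on the contrast.

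For a nominal .10 test under assumed decay (A to D):
- 12 months against baseline: about .14-.20, or .12-.17 with the smaller baseline SD
- linear trend: about .155-.22, or .14-.20 with the smaller baseline SD
- 3 months against baseline: about .03-.07, which is conservative
- 3-df component-by-time test: about .10-.115

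Weaker decay gives less (E, equal SDs: .122, .129 and .083 for 12 months, trend and 3 months). Constant correlation and variance give none. Because the article leaves the deciding contrast open, it does not confine itself to the safer tests. This is something that should be fixed, not a fault that invalidates the design.

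**What to change.** Replace the random-intercept sentence with text on these lines: within-person covariance over the four visits is unstructured, fitted by REML with Kenward-Roger degrees of freedom; if the fit does not converge, a named simpler structure is used. Because the visits are unequally spaced, the fallback should depend on months apart, not visit number. Apply the same covariance to the total-effect test.

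State also whether time is categorical or linear, and which time contrast (a named visit, a trend, or the 3-df test) decides component selection.

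The cost is small. Four visits need ten covariance parameters (4 variances + 6 covariances) instead of two, with 180 participants. The unstructured form contains the random-intercept pattern as a special case, so little is lost if that pattern is right. The remaining risk is a small chance of non-convergence, which the fallback covers. Trial conduct and sample size do not change.
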